## Methods

### Aims, design and setting

The TANGO-DM trial (randomized trial of effective treatment according to new GDM criteria) will evaluate the effectiveness of intensive GDM treatment as compared to normal obstetric care in pregnant women with a discordant OGTT result between the new (2013) WHO criteria as compared to the old (1999) criteria. This study will be conducted as an open label multicenter randomized controlled trial (RCT), applying an individual-randomization strategy. The study will be conducted within the framework Dutch Consortium for Healthcare Evaluation and Research in Obstetrics and Gynaecology – NVOG Consortium 2.0, a collaborative network of all major hospitals in the Netherlands and the Dutch Society of Obstetrics and Gynaecology (NVOG). The trial has been approved by the Medical Research Ethics Committee of the Amsterdam UMC, location AMC (METC 2018_173). The trial is registered at the Central Committee on Research Involving Human Subjects (CCMO) on 22 September 2018 under number NL63013.018.18 [20].

### Participants and eligibility criteria

A flowchart is shown in Fig. 1.

**Fig. 1 Fig1:**
[figure not shown]
Consort flow diagram

Women are eligible if they have a singleton pregnancy, with a gestational age between 16 + 0 and 32 + 0 weeks at study entry, aged *≥* 18 years, without pre-conceptional diabetes, a major fetal congenital abnormality, or significant medical or psychiatric co-morbidities as judged by the investigator (e.g., high dose corticosteroid treatment), with the ability to understand the informed consent form. In addition, participants will need to have undergone a 2- or 3-point 75-gram OGTT, consisting of a fasting, 1 h (in case of 3-point OGTT) and 2 h post load glucose concentration via venipuncture, conducted between gestational ages 16 + 0 and 30 + 0 weeks yielding glucose concentrations discordant between the old WHO (1999) and the new WHO (2013) criteria.

A discordant result is defined as any single blood glucose concentration during a 75-gram venous blood OGTT within the following ranges, in the absence of any other glucose concentration exceeding the upper limit of discordancy (Table 1). For example, a pregnant individual is eligible if she has a fasting glucose between 5.1 mmol/l and 7.0 mmol/l, as long as the 2-hour glucose is below 8.5 mmol/l. Similarly, a pregnant individual with a 2-hour glucose between 7.8 mmol/l and 8.5 mmol/l is eligible, as long as the fasting glucose is < 7.0 mmol/l.

**Table 1 Tab1:** Glucose cut of values

	WHO 2013	WHO 1999
Fasting glucose	≥ 5.1 mmol/l	< 7.0 mmol/l
1-hour glucose	≥ 10 mmol/l	
2-hour glucose	< 8.5 mmol/l	≥ 7.8 mmol/l

As recommended by the Guideline ‘Diabetes in Pregnancy’ of the Dutch Society of Gynaecology and Obstetrics (NVOG) and the Royal Dutch Organisation of Midwives (Koninklijke Nederlandse Organisatie van Verloskundigen (KNOV)), obstetricians and midwives in the Netherlands screen for GDM between 24 and 28 weeks gestational age (or 16 weeks of gestation in case of history of GDM) using a risk-based, 1-step screening strategy [6]. Risk factors for GDM are defined in the guideline as: family history of diabetes mellitus in a first degree relative; history of GDM, history of LGA or macrosomia > 4.5 kg; obesity (body mass index (BMI) > 30 kg/m^2)^; polycystic ovarian syndrome (PCOS); ethnicity (established by self-identification) associated with high GDM prevalence (e.g. Afro-Caribbean, Hindu-Surinamese, South-Asian, Middle-Eastern, Moroccan, Egyptian) and a history of unexplained stillbirth. Furthermore, clinical symptoms (e.g. polyuria, polydipsia, suspected macrosomia and/or hydramnios) suggestive of diabetes, are to trigger an oral glucose tolerance test.

Although there is wide uptake of the risk factor-based screening strategy in the Netherlands, clinicians are at liberty to apply different screening strategies at their discretion or upon patient request, without affecting eligibility.

The study will be executed in healthcare settings with both mid/high risk pregnancies (hospital antenatal care) and low risk pregnancies (community midwife antenatal care).

### Recruitment and study procedure

A flowchart is shown in Fig. 2.

**Fig. 2 Fig2:**
[figure not shown]
Flowchart screening and study procedures

Eligible patients will be informed and invited to participate by either their diabetes care or obstetric care provider, i.e. physician, obstetrician, midwife, or diabetes nurse. Following counselling, written informed consent is obtained. Sufficient recruitment depends on the applicability of our assumptions of the number of pregnant women with discordant OGTT results. Based on work from the Netherlands, a conservative estimate of the percentage of women with a discordant blood glucose concentration after OGTT is around 9–15% [21].

Participants of the study will be randomized between:Intensive GDM treatmentNormal obstetric care

#### Intensive GDM treatment

Participants randomized to intensive treatment will be counselled on the diagnosis of GDM and conventional GDM treatment will be initiated. Treatment will comply with the national guideline for GDM [22] and will include:

Self-monitoring of blood glucose (target values: fasting *≤* 5.3, 1-hour postprandial *≤* 7.8 and/or *≤* 6.7mmol/l), or target values according to local protocol (e.g. 1.5-hour postprandial < 7 mmol/l). The recommended frequency for blood glucose measurements is (initially) daily, four times a day.Dietary recommendations [23].Pharmacotherapy for those unable to achieve euglycemia with dietary intervention alone: guidelines in the Netherlands suggest insulin as a first choice; oral antihyperglycemic agents are optional at the clinician’s discretion [6].

Mode and timing of delivery, postpartum advice, and postpartum screening for neonatal hypoglycaemia will be conducted based on the NVOG guideline for GDM and/or local protocol. Additional ultrasounds and induction of labor could be part of the intervention, but are not mandatory according to national guidance, which does recommend induction of labor before 39 weeks gestational age in case of GDM requiring medication. Postpartum recommendations after GDM include annual visits at the general practitioner to rule out diabetes type 2. Furthermore, in subsequent pregnancies after GDM, early OGTT screening is offered at 16 weeks, in addition to routine screening at 24–28 weeks.

In addition to the indications in standard care, postpartum screening for neonatal hypoglycaemia is recommended only for infants of GDM mothers treated with insulin or oral antihyperglycemic agents. Diet controlled GDM is not considered a routine indication for neonatal hypoglycemia screening [6].

#### Normal obstetric care

Participants randomized to normal obstetric care will receive maternity care by their usual care provider (midwife or obstetrician, as appropriate), according to common practice, local protocol and/or national guidelines [24, 25] for the duration of the pregnancy, birth and postpartum period. This includes that advice regarding future pregnancies, glucose testing and neonatal screening for hypoglycemia will only be offered in case of risk factors including macrosomia or small for gestational age. In contrast to intensive GDM care, in future pregnancies, early screening for GDM will not be advised, and yearly checkups at the general practitioner to rule out type 2 diabetes will not be indicated.

For participants randomized to normal obstetric care, who have been randomized early in pregnancy (16–20 weeks) and who have been tested because of a prior pregnancy complicated by GDM, a repeat OGTT will be carried out at 24–28 weeks of gestational age as part of routine antenatal care. Alternatively, a clinical indication may arise to repeat the OGTT later in pregnancy, for instance because of clinical symptoms. Among participants allocated to normal obstetric care, when glucose values are normal or discordant, normal obstetric care will be continued. Glucose values exceeding the discordant results (fasting *≥* 7.0 OR 2-hour post load glucose value *≥* 8.5 mmol/l) will result in initiation of GDM treatment (see Figs. 1 and 2), which will result in appropriate recommendations for future pregnancies, postnatal screening for diabetes type 2 and may include neonatal hypoglycemia screening.

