Based on the 2013 WHO thresholds, an additional group of pregnant women with mild hyperglycemia, formerly labeled as normal glucose tolerance, are now classified as having GDM and will be advised treatment. As a result of adding the 1-hour value, there is a group of women who would not have been diagnosed because the 1-hour blood draw did not exist in the WHO 1999 guideline. In addition, there is a group of women formerly labeled as having GDM who are now classified as normal glucose tolerance. Hillier et al. showed that expanded criteria for GDM might almost double the incidence of GDM without lowering risk in adverse pregnancy outcome [12]. The recent GEMS trial showed similar results in a large group of women who were randomized with the use of lower or higher glycemic criteria for diagnosis. However, on closer examination of the GEMS subgroup analyses among participants with OGTT results discordant between the higher and lower criteria, allocation to intensive GDM treatment was found to lead to a large reduction in large for gestational age infants. The fact that the GEMS trial was not designed to investigate this discordant group hampers interpretation of this particular finding, which may be of relevance to individual patients [13]. Therefore, to date, there is no evidence from well-designed randomized trials, that treatment of GDM diagnosed by the new (2013) WHO criteria, but not by the old (1999) criteria, leads to improved perinatal and maternal outcomes. Thus, benefits and harms, and cost-effectiveness of adopting these new criteria are currently unknown [14–16].

The new (2013) WHO criteria have now been implemented in many, but not all, countries [17, 18]. The Netherlands, along with other European countries including the United Kingdom, Sweden, Denmark and Belgium, had, up until the start of this study (2018), not implemented the WHO 2013 criteria [19]. Since then, Sweden has implemented the WHO 2013 criteria, and Belgium has introduced a two-step method, in which at the second test the diagnosis is made with the WHO 2013 criteria.

There is thus an immediate and short-lived window of opportunity to assess the potential health benefits and economic costs of the WHO 2013 criteria.

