### Analyses and reporting of results

#### General outline of analysis

The intention-To-Treat (ITT) population will consist of all eligible participants who gave consent and have been allocated to one of the two treatments, irrespective of treatment received. The per protocol population is defined as all participant who received the allocated treatment. The per protocol population includes those who initiated treatment for GDM as allocated following randomization and who completed the treatment until delivery, as well as those receiving normal antenatal care after having been allocated to the normal antenatal care group. If, in the course of normal antenatal care, a repeat OGTT was deemed necessary, and this repeat OGTT indicated a diagnosis according to both old and new GDM criteria, GDM treatment should be initiated as a part of normal antenatal care, and would not be a reason for a participant to be excluded from the per protocol analyses.

Participants who did not initiate GDM treatment when they had been allocated to GDM treatment, will be removed from the per-protocol population.

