#### Planned analyses

Baseline characteristics will be presented as frequencies and percentages in each group, or as averages (mean or median) with standard deviations or interquartile ranges as appropriate. The primary outcome will be evaluated by estimating the relative risk between both treatment arms. Analyses will be conducted in both the intention-to-treat and per protocol population for the primary outcome.

Relative risks will be estimated for categorical outcomes, with 95% confidence intervals, and χ2 tests for significance. Fisher’s exact test will be used for sparse events where assumptions of the χ2 test are not met. Continuous data will be described as means with standard deviation if normally distributed, or medians with interquartile ranges when not normally distributed; tests for significance are t-tests or Mann-Whitney U tests, respectively. The Hodges-Lehman estimator will be used to calculate the confidence interval for the difference in medians.

Individuals who were randomized to normal obstetric care but for unknown reasons received treatment they will be excluded from the per protocol analysis. If the treatment followed an abnormal repeat OGTT they will remain in the per protocol analysis. Individuals who were randomized to GDM treatment but for unknown reasons never received treatment will be excluded from the per protocol analysis. If, per example, they did not receive treatment because of preterm birth they will remain in the per protocol analysis.

Subgroup analyses will be performed for BMI (under or above 30 kg/m2), early or late GDM (before or after 24 weeks) and according to the result of the OGTT (abnormal fasting result, abnormal postprandial result, or both).

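### For one band of repeat-OGTT results in controls, the care section continues normal care and the per-protocol definition starts GDM treatment

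*Protocol article*

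**What the plan says.** Four places in the protocol article bear on a control who has a repeat OGTT.

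- **Participants and eligibility criteria (with Table 1)** defines discordance value by value. One value in a listed range is enough, "in the absence of any other glucose concentration exceeding the upper limit of discordancy". Two examples follow. One is a "fasting glucose between 5.1 mmol/l and 7.0 mmol/l, as long as the 2-hour glucose is below 8.5 mmol/l". The other is that a woman with a "2-hour glucose between 7.8 mmol/l and 8.5 mmol/l is eligible, as long as the fasting glucose is < 7.0 mmol/l".
- **Normal obstetric care** says who is retested: routinely, controls randomised at 16–20 weeks who were tested because of prior GDM; otherwise, controls with a clinical indication. It then gives the rule: "when glucose values are normal or discordant, normal obstetric care will be continued". Treatment starts at fasting ≥ 7.0 or 2-hour ≥ 8.5 mmol/l.
- **General outline of analysis**, in defining the per-protocol population, says that if "this repeat OGTT indicated a diagnosis according to both old and new GDM criteria, GDM treatment should be initiated" as part of normal antenatal care. Such a woman is not excluded from the per-protocol analysis.
- **Planned analyses** says of treated controls: "If the treatment followed an abnormal repeat OGTT they will remain in the per protocol analysis". It gives no glucose values for an abnormal result.

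**The concern.** Discordant, as the article defines it, does not mean diagnosed by exactly one set of criteria. The definition works on single values, so a woman can have one value that meets only the 2013 criteria and another that meets only the 1999 criteria. She is then discordant by definition and also diagnosed by both sets. For her, the care section and the analysis section give opposite instructions.

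Three things depend on the answer: the care she receives, whether a treated control dilutes the comparison between arms, and whether she counts as per-protocol. The per-protocol analysis is planned for the primary outcome, and the trial is open label and multicentre.

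**Working it through.** **1. The two rules, using the article's own cut-offs (mmol/l)**

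- Normal obstetric care: treat if fasting ≥ 7.0 or 2-hour ≥ 8.5.
- General outline of analysis: treat if (fasting ≥ 7.0 or 2-hour ≥ 7.8, the 1999 criteria) and (fasting ≥ 5.1 or 1-hour ≥ 10 or 2-hour ≥ 8.5, the 2013 criteria). The 1-hour value counts only towards 2013, because "the 1-hour blood draw did not exist in the WHO 1999 guideline".

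**2. Comparison over a grid**

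Both rules were evaluated in 0.1 steps for fasting 3.5–8.9 and 2-hour 5.0–10.9, with the 1-hour value absent, below 10, or at least 10. That gives 55 × 60 × 3 = 9,900 combinations.

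| | Analysis section: treat | Analysis section: do not treat |
|---|---|---|
| Care section: treat | 6,225 | 0 |
| Care section: do not treat | 511 | 3,164 |

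These are grid cells, not frequencies of patients. The care rule never treats a result that the analysis rule leaves untreated. All 511 disagreements have a 2-hour value of 7.8–8.4 and fasting below 7.0:

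- fasting 5.1–6.9, any 1-hour state: 19 × 7 × 3 = 399
- fasting below 5.1 with 1-hour ≥ 10: 16 × 7 = 112

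**3. One result followed through: fasting 5.5, 2-hour 8.0**

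- Eligibility definition: fasting lies in its range and the 2-hour value is below 8.5, so the result is discordant.
- Normal obstetric care: discordant, so normal care continues.
- General outline of analysis: the 2-hour value meets 1999 (≥ 7.8) and fasting meets 2013 (≥ 5.1), so treatment starts.

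The band is not hypothetical. Planned analyses includes an OGTT subgroup of women abnormal on both fasting and postprandial values.

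**4. Per-protocol status**

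If this woman is treated, General outline of analysis keeps her in the per-protocol set, but by Normal obstetric care she has departed from the control strategy. Planned analyses does not settle this. It uses abnormal without values, and it uses the same word in the OGTT subgroups for qualifying results, all of which are discordant. Read that way, even a control treated after a repeat that is diagnostic by only one set of criteria could be retained.

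**5. Size for the intention-to-treat comparison**

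Inputs from Sample size and the abstract: 16% against 10%, alpha 5% (two-sided assumed), 80% power, 5% loss, 516 per group.

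The plan's figure first, with pooled variance under the null and mean rate 0.13:

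n = [1.96 × √(2 × 0.13 × 0.87) + 0.842 × √(0.16 × 0.84 + 0.10 × 0.90)]² / 0.06² = 492 per arm

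492 / 0.95 = 518, against 516 stated, so the figure reproduces closely. Evaluable per arm: 516 × 0.95 ≈ 490.

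If a share q of controls is treated only because of the conflict, and treatment has its full assumed effect, the control rate becomes 16% − 6% × q. With p₁ the control rate, p₂ = 0.10, p̄ their mean and n = 490:

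power = Φ{[(p₁ − p₂) − 1.96 × √(2p̄(1 − p̄)/n)] / √[(p₁(1 − p₁) + p₂(1 − p₂))/n]}

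| q (assumed) | Women of 516 | Control rate | Power |
|---|---|---|---|
| 0% | 0 | 16.00% | 79.8% |
| 1% | about 5 | 15.94% | 79.1% |
| 2% | about 10 | 15.88% | 78.4% |

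**The case against.** The strongest reply is that Normal obstetric care holds the operative rule. It is where sites look for management, it gives numbers, it agrees with the eligibility definition, and it points to Figs. 1 and 2, which could not be checked here. On this view the analysis section's reference to both criteria is loose shorthand for no longer discordant. That may be what was meant. It does not remove the conflict, because the sentence says that treatment should be started and it is the text that decides who is per-protocol. Nor is this a detail left to a fuller document: the article states both rules.

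Other parts of the reply stand and limit the point.

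- A reader might infer a third treatment rule from Planned analyses. There is none. That sentence starts no treatment; it only classifies women already treated. The fault there is an undefined term.
- A reader might infer a substantial loss of power. With 5% or 10% of controls treated, the same formula gives 76.1% or 71.9%. But that is about 26 or 52 of 516 controls, each needing a repeat test that falls in the band, and nothing in the article supports such shares for this conflict. Controls at fasting ≥ 7.0 or 2-hour ≥ 8.5 are treated under both rules, so any dilution from them is not due to it. Even the 1–2% figures assume the full effect from treatment begun only after the repeat test.
- A reader might infer that sites have already managed identical results differently. The article documents no such case.
- Membership of the intention-to-treat population is the same under either rule.

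**Conclusion.** The contradiction is real and follows from the article's own thresholds alone. It is confined to controls with a repeat OGTT whose 2-hour value is 7.8–8.4 and fasting below 7.0, with fasting 5.1–6.9 or a 1-hour value ≥ 10. Every other result gets the same instruction from both sections. Because the number of women in the band is not given, the loss of about 0.7 to 1.4 percentage points of power (79.8% to 79.1–78.4%) is an illustration resting on an assumed 1–2% share and a full 16%-to-10% effect. The case does not rest on power. It rests on one test result receiving opposite treatment instructions and an unsettled per-protocol status. Severity is moderate.

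**What to change.** The sponsor should reconcile Normal obstetric care, General outline of analysis and Planned analyses into a single repeat-OGTT rule. It should be written in glucose values and say explicitly what a 1-hour value ≥ 10 means when the 2-hour value is 7.8–8.4. The per-protocol definition should repeat that wording, so that abnormal no longer stands undefined. It should also state the per-protocol status of a control treated after a result that the rule does not treat, and of a control left untreated after a result that it does.

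Any retested controls found in the band should then be classified the same way in both descriptions of the per-protocol population. Which clinical rule applies is for the sponsor.

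The cost is a clarifying amendment, a letter to sites and a check of repeat-OGTT values in the control arm. No new data collection is needed, and the sample size is unaffected.

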#### Questionnaires

For all participants in the Tango-DM trial, questionnaires will be administered at 3 time points: study inclusion, around 36 weeks of pregnancy and 4–6 weeks postpartum.

Quality of life will be measured using the EuroQol (EQ-5D-5 L) at a gestational age of 36 weeks and 6 weeks post-partum. The EQ-5D-5 L assesses 5 domains (mobility, self-care, usual activities, pain/discomfort, anxiety/depression) with 5 possible answer levels ranging from “no problems” to “severe problems” [26].

Mood will be scored using the Edinburgh Postnatal Depression Scale (EPDS) at inclusion and post-partum. The EPDS has 7 questions regarding depression and anxiety [27].

The questionnaires will take approximately 10–30 min to complete.

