### Cost-effectiveness

The aim of the economic evaluation is to assess the incremental costs and the incremental health effects of intensive GDM treatment as compared to normal obstetric care in participants. Both a cost-effectiveness analysis (CEA) and a cost-utility analysis (CUA) will be performed from a societal and healthcare perspective according to Dutch guidelines [30] from diagnosis of GDM until 6 weeks postpartum. Because the time horizon of the economic evaluation is less than 12 months, discounting is not necessary.

Costs will be measured from a societal perspective using (web-based) questionnaires adapted from the iMTA Medical and Productivity Cost Questionnaires at a gestational age of 36 weeks and 6 weeks postpartum [26, 31]. Cost categories that will be included are: (1) healthcare costs (primary and secondary care, complementary cares and home care) (2) lost productivity costs (absenteeism from paid and unpaid work, and presentism) and (3) patient costs (informal care and other care services paid for by patients themselves). Valuation will be done according to Dutch costing guidelines [32]. For the valuation of health care utilization, lost productivity and informal care, Dutch standard costs will be used. Medication use will be valued using prices of the Royal Dutch Society for Pharmacy. Patient and family costs other than informal care will be valued using self-reported prices. For the valuation of absenteeism from paid work, the friction cost approach will be used.

The following effect measures will be included in the economic evaluation:LGA (birth weight > 90th percentile)Perinatal and maternal outcomes as stated in the section aboveQuality-Adjusted Life-Years (EuroQol (EQ-5D-5 L) with Dutch reference values) [31]

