### Burden of treatment

We anticipate that the treated group will perceive their pregnancies as more intrusive and potentially harbor negative sentiments towards their pregnancies in contrast to women receiving standard obstetric care. With the Quality-Adjusted Life-Years (EuroQol (EQ-5D-5 L) with Dutch reference values) and the Social support questionnaire (SSQ, send 6 weeks post-partum) we will evaluate the differences between the treated and untreated group.

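### QALYs are to run from GDM diagnosis to 6 weeks postpartum, but EQ-5D-5L is first measured at 36 weeks, so about half the period has no utility data at usual screening times

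*Protocol article*

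**What the plan says.** The Cost-effectiveness section plans a cost-effectiveness and a cost-utility analysis "according to Dutch guidelines [30] from diagnosis of GDM until 6 weeks postpartum". Its effect measures include QALYs derived from EQ-5D-5L, and the Burden of treatment section uses the same measure, "Quality-Adjusted Life-Years (EuroQol (EQ-5D-5 L) with Dutch reference values", to compare the treated and untreated groups.

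The Questionnaires section gives the contacts: "questionnaires will be administered at 3 time points: study inclusion, around 36 weeks of pregnancy and 4–6 weeks postpartum". It then assigns instruments to times. For utility: "Quality of life will be measured using the EuroQol (EQ-5D-5 L) at a gestational age of 36 weeks and 6 weeks post-partum". For mood: "Mood will be scored using the Edinburgh Postnatal Depression Scale (EPDS) at inclusion and post-partum". So the inclusion contact exists and carries EPDS, but EQ-5D-5L is not among the measures named for it.

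Under Participants and eligibility criteria, the qualifying OGTT is "conducted between gestational ages 16 + 0 and 30 + 0 weeks", and women enter "with a gestational age between 16 + 0 and 32 + 0 weeks at study entry". The same section puts usual screening at 24–28 weeks, or at 16 weeks for women with a history of GDM.

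The remainder of the Cost-effectiveness section imputes missing costs and effects by MICE and adjusts differences for confounders where needed. It does not name baseline utility, and it does not say how the QALY is formed before 36 weeks.

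**The concern.** A QALY over a stated period needs a utility value at or near the start of that period. Here the start is diagnosis, and the first value may come many weeks later. In between, women in the intensive arm receive the diagnosis, change their diet, begin self-monitoring (recommended four times a day at first) and, for some, begin medication. The Burden of treatment section expects the treated group to find pregnancy more intrusive. Its other instrument, the Social support questionnaire, is sent only at 6 weeks postpartum. Neither instrument records how the first weeks of treatment were experienced.

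The incremental QALY, the cost per QALY and the QALY acceptability curves would therefore rest partly on an assumption that the plan does not state. An analysis plan written later cannot repair this, because the data would not have been collected.

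**Working it through.** The plan gives no figure for how much of the QALY period its utility measurements cover, so there is nothing to reproduce first.

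**Inputs from the protocol article.** First EQ-5D-5L at 36 weeks; end of horizon at 6 weeks postpartum; start of horizon at diagnosis, taken as the qualifying OGTT, 16 to 30 weeks; usual screening at 24–28 weeks.

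**Assumption.** Birth at 40 weeks, varied from 37 to 42.

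**Share of the QALY period before the first utility value**, with diagnosis at week d and birth at week b: (36 − d) / (b + 6 − d).

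| Diagnosis (week) | Birth at 40 weeks | Birth at 42 to 37 weeks |
|---|---|---|
| 16 | 20/30 = 66.7% | 62.5% to 74.1% |
| 24 | 12/22 = 54.5% | 50.0% to 63.2% |
| 26 | 10/20 = 50.0% | 45.5% to 58.8% |
| 28 | 8/18 = 44.4% | 40.0% to 53.3% |
| 30 | 6/16 = 37.5% | 33.3% to 46.2% |

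Women who deliver before 36 weeks have no antenatal utility value at all.

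**Can the planned methods fill the gap?** MICE draws a missing value from its relation to other variables among participants in whom it was observed. Baseline EQ-5D-5L is observed in nobody, so that relation cannot be estimated. Baseline EPDS and clinical covariates are available only as proxies. Carrying the 36-week value back would apply a value measured on treatment to the time before treatment began.

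**What a chance baseline difference is worth.** Take a difference of 0.01 in mean utility, diagnosis at 26 weeks and birth at 40.

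- Trapezoidal area under the curve: baseline utility carries half the interval to 36 weeks, that is 10/2 = 5 weeks, or 5/20 = 25% of the weight. Its direct contribution is 0.01 × 5/52 = 0.00096, about 0.001 QALY. For diagnosis at 16 weeks it is 0.01 × 10/52 = 0.0019; at 30 weeks, 0.01 × 3/52 = 0.0006.
- Full persistence to 6 weeks postpartum: 0.01 × 20/52 = 0.0038, about 0.004 QALY.

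**Is 0.01 a reasonable illustration?** The article gives no standard deviation for utility. Assuming 0.10 to 0.20, and 516 × 0.95 = 490 women per arm, the standard error of a baseline difference is SD × √(2/490) = 0.0064 to 0.0128. So 0.01 is about 0.8 to 1.6 standard errors, well within chance.

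**The case against.** Randomization is the strongest reply. Expected baseline utility is equal in the two arms, and a chance difference is part of the sampling uncertainty that the bootstrap intervals and acceptability curves already express. An incremental QALY needs only the difference between arms, so one can start both arms at the same level and interpolate to the observed difference at 36 weeks. This stands. A reader might infer that chance baseline differences bias the QALY result; the design does not support that. What remains is lost precision, and a path before 36 weeks that is assumed and not observed.

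A second reply is that treatment continues until delivery, so the 36-week value is taken on treatment and captures continuing burden. This also stands. A reader might infer that the unmeasured weeks are when the arms differ most. The note that monitoring is four times a day at first makes an early peak possible, but nothing in the article shows one.

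Third, the effect is confined to one of several effect measures in a secondary economic evaluation. That is correct.

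A last reply is that the article condenses a fuller protocol. But it gives the utility schedule explicitly, instrument by instrument, and the stated times do not cover the stated horizon. If the full protocol does schedule EQ-5D-5L at inclusion, the article needs correcting.

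**Conclusion.** The mismatch holds. As written, the first 44–55% of the QALY period has no utility data for women diagnosed at 24–28 weeks, with birth at 40 weeks assumed. The figure of two-thirds belongs to diagnosis at 16 weeks, which under the guideline means mainly women with prior GDM. It is neither typical nor a strict ceiling, since birth at 37 weeks gives 74%.

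The consequences are an unmeasured early treatment effect on quality of life, no antenatal value for births before 36 weeks, and no baseline utility with which to gain precision or adjust for chance imbalance. A baseline difference of 0.01 matters by about 0.001 QALY for diagnosis at 26 weeks, and by about 0.004 only if it persisted undiminished over the whole period. One might infer that such an amount could swamp the true QALY difference, but the article gives no expected QALY difference to compare it with.

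LGA, the sample size and cost per LGA avoided are untouched.

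**What to change.** Add EQ-5D-5L to the existing inclusion questionnaire, completed before the woman knows her allocation. Compute QALYs by area under the curve from inclusion, and estimate the difference between arms by regression adjusted for baseline utility. The only stretch then left without a value at its start is any lag between the OGTT and inclusion.

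For women already enrolled without a baseline value, state the assumption used before 36 weeks, for example equal mean baseline utility in both arms with linear change to 36 weeks, and vary it in sensitivity analyses. If a cost per QALY is also reported for 36 weeks to 6 weeks postpartum only, count costs over those same weeks; otherwise its numerator and denominator cover different periods.

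The cost is five more items at a contact already made and a minor amendment. The amendment cannot supply baseline values for women already enrolled, so for them the stated assumption and its sensitivity analyses are all that can be offered.
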